i*Abnormal pure tone audiometry in at least one ear:* a dichotomous outcome of whether the child has abnormal pure tone audiometry. If testing by pure tone audiometry is not possible, sound field audiometry can be used in its place. Abnormal audiometry in at least one ear is indicated by a measurement of > 20 dB HL using the pure tone method, > 25 dB HL for sound field, for at least one of four frequencies tested: 500 Hz, 1000 Hz, 2000 Hz, or 4000 Hz.j*Abnormal pure tone audiometry in both ears:* a dichotomous outcome defined in the same way as secondary outcome 7bi, for patients who have both ears tested and both tested ears indicate abnormal audiometry.k*Severity of better ear:* a short ordinal outcome of the severity of the better ear. If testing by pure tone audiometry is not possible, sound field audiometry can be used in its place. Each patient will be classified according to the average score in the better ear if pure tone, or both ears if sound field, across the four frequencies (500 Hz, 1000 Hz, 2000 Hz, or 4000 Hz) to the categories in Table 2 [14].*Middle ear function:*
a*Flat line tympanogram in at least one ear:* a dichotomous outcome of whether the child has flat line tympanogram, assessed at age 12 months, 3 years, and 5 years. Children with either ear measured as “Type B” will be classified as having flat line tympanogram in at least one ear.b*Flat line tympanogram in both ears:* a dichotomous outcome of whether the child has flat line tympanogram, assessed at age 12 months, 3 years, and 5 years. Children with both ears measured as “Type B” will be classified as having flat line tympanogram in both ears.*Dentofacial development at age 5 years:*
a*Soft tissue ANB angle:* a continuous outcome of the angle between soft tissue nasion (points A and B) measured using a profile photograph [15].b*Maxillary arch constriction score:* a bounded continuous outcome, measured using the Huddart/Bodenham scoring system, on a maxilliary and mandibular arch impression. A score can range from − 24 to 8 and is measured in whole numbers [16, 17]*.**Growth at 12 months:*
a*Nude weight:* a continuous outcome, measured in grammes and recorded to the nearest whole number.b*Crown to heel length:* a continuous outcome, measured in centimetres and recorded to one decimal place.c*Occipitofrontal circumference:* a continuous outcome, measured in centimetres and recorded to one decimal place.

**Table 2 Tab2:** Classifying severity in better ear

Average dB HL	Severity

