≤ 20 dB HL	Normal
Between 21 and 40 dB HL	Mild
Between 41 and 70 dB HL	Moderate
Between 71 and 95 dB HL	Severe
> 95 dB HL	Profound

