#### Analysis of secondary outcomes

Analysis approaches for each secondary outcome are dependent on the type of outcome; Table 6 provides a summary.

**Table 6 Tab6:** Endpoint type for secondary outcomes

Outcome type	Outcome
Dichotomous	1b: Insufficient velopharyngeal function (VPC rate) at 5 years
	2a: Insufficient velopharyngeal function (VPC rate) at 3 years
	3a: Canonical babbling present at 12 months
	6a: Postoperative dehiscence
	6b: Postoperative infection
	6c: Evidence of fistula
	7ai: Abnormal Transient Otoacoustic Emission (TEOAE) at 12 months
	7aii: Abnormal sound field audiometry at 12 months
	7bi_1: Abnormal pure tone audiometry in at least one ear at 3 years
	7bi_2: Abnormal pure tone audiometry in at least one ear at 5 years
	7bii_1: Abnormal pure tone audiometry in both ears at 3 years
	7bii_2: Abnormal pure tone audiometry in both ears at 5 years
	8a_1: Flat line tympanogram in at least one ear at 12 months
	8a_2: Flat line tympanogram in at least one ear at 3 years
	8a_3: Flat line tympanogram in at least one ear at 5 years
	8b_1: Flat line tympanogram in both ears at 12 months
	8b_2: Flat line tympanogram in both ears at 3 years
	8b_3: Flat line tympanogram in both ears at 5 years
Short ordinal	7biii_1: Severity of better ear at 3 years
	7biii_2: Severity of better ear at 5 years
Long ordinal	1a: Velopharyngeal composite score summary (VPC sum) at 5 years
Bounded continuous	2b: Velopharyngeal insufficiency symptoms at 3 years
	3b: Canonical babbling ratio at 12 months
	4a: Percent consonants correct (PCC) at 3 years
	4b: Percent correct placement (PCP) at 3 years
	4c: Percent correct manner (PCM) at 3 years
	4d: Non-oral consonant errors at 3 years
	4e: Oral consonant errors at 3 years
	5a: Percent consonants correct (PCC) at 5 years
	5b: Percent correct placement (PCP) at 5 years
	5c: Percent correct manner (PCM) at 5 years
	5d: Non-oral consonant errors at 5 years
	5e: Oral consonant errors at 5 years
	9b: Maxillary arch constriction score at 5 years
Continuous	3c: Consonant inventory at 12 months
	9a: Soft tissue ANB angle at 5 years
	10a: Nude weight at 12 months
	10b: Crown to heel length at 12 months
	10c: Occipitofrontal circumference at 12 months

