##### Dichotomous outcomes

For outcomes of this type, see Table 6, the number of participants categorised as having, or not having, the outcome of interest will be summarised overall, for each randomised group by frequencies and percentages. The numbers with the outcome between the randomised groups will be compared using a chi-squared test, with the relative risk [20] and 95% CI also reported.

In the circumstance that the expected number of participants with and without the outcome for each randomised group contains less than five participants, thereby raising concerns over the appropriateness of a chi-squared test, then Fisher’s exact test will be used.

No sensitivity analysis will be performed.

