##### Short ordinal outcomes

For outcomes of this type, see Table 6, the number of participants who are categorised into each classification of interest will be summarised overall, for each randomised group by frequencies and percentages. The numbers with the outcome between the randomised groups will be compared using a chi-squared test for trend.

In the circumstance that the expected number of participants in each classification for each randomised group contains less than five participants, thereby raising concerns over the appropriateness of a chi-squared test for trend, an alternative appropriate analysis approach will be used, e.g. combining like groups or applying a proportional odds model.

No sensitivity analysis will be performed.

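### Average hearing level at 3 and 5 years is compared only in severity bands, by a trend test with no effect measure or confidence interval, so a null result cannot say which hearing differences are excluded.

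*SAP article*

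**What the plan says.** The SAP article defines three hearing outcomes at 3 and 5 years (Secondary outcomes, item 7b; labels as in Table 6).

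- **7bi and 7bii** are yes/no outcomes for at least one ear and for both ears. They depend on any one of four frequencies, not on the average: "Abnormal audiometry in at least one ear is indicated by a measurement of > 20 dB HL using the pure tone method", with a limit of 25 dB HL for sound field. The Dichotomous outcomes section compares them by chi-squared test, "with the relative risk [20] and 95% CI also reported".
- **7biii** uses the average over the four frequencies: "Each patient will be classified according to the average score in the better ear if pure tone, or both ears if sound field". Table 2 has five bands: up to 20 dB HL, then "Between 21 and 40 dB HL", 41 to 70, 71 to 95, and above 95.

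Table 6 lists 7biii only under short ordinal outcomes ("7biii_1: Severity of better ear at 3 years", with a matching row for 5 years). For that type the plan gives frequencies and percentages by group and one test: "The numbers with the outcome between the randomised groups will be compared using a chi-squared test for trend". If expected counts fall below five, "an alternative appropriate analysis approach will be used, e.g. combining like groups or applying a proportional odds model". No row of Table 6 carries the average itself.

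**The concern.** Hearing level is a named secondary objective. The plan measures it on a dB scale, computes the average for each child, and uses that average only to assign a band. Movement within a band is invisible to the 7biii test. Because no effect measure or interval is named, a non-significant result could mean that timing of surgery leaves hearing much the same, or that the bands were too coarse to tell. A reader could not separate the two.

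Elsewhere the plan keeps the scale. Under Long ordinal, bounded continuous, and continuous outcomes it compares weight, length, ANB angle, the canonical babbling ratio and the seven-point VPC sum by t test or a non-parametric equivalent, with a 95% CI. Canonical babbling and 5-year velopharyngeal function each have both a cut and a full-scale measure. No reason is given for treating hearing differently.

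**Working it through.** **The plan's own figures.** None concerns hearing: there is no power, mean, SD or band distribution. The only power calculation is for the primary outcome, and it reproduces: [1.96 × √(2 × 0.345 × 0.655) + 0.842 × √(0.40 × 0.60 + 0.29 × 0.71)]² / 0.11² = 292 per arm.

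**Numbers available.** 558 recruited (Trial status), allocated 1:1, gives 279 per arm. Less the 10% attrition in Sample size, this is 279 × 0.9 = 251 per arm. A band needs 5/251 = 2.0% of children for an expected count of five.

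**What each 7b outcome reports**

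| Outcome | Uses | Test | Effect measure named |
|---|---|---|---|
| 7bi, 7bii | any single frequency over its limit | chi-squared | relative risk, 95% CI |
| 7biii | four-frequency average, banded | trend test | none |

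This part needs no assumption.

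**Power, scenario A: the whole distribution shifts (assumed).** Set the shift so that comparing means has 80% power: d = (1.960 + 0.842) × SD × √(2/251). Find the band shares in each arm, with cuts at 20.5, 40.5, 70.5 and 95.5. Score the bands 0 to 4. Then z = (difference in mean score) / √(2 × variance of score / 251), and power = Φ(z − 1.96).

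Example: normal, mean 20, SD 10, the arms placed d/2 either side of the mean.
- d = 2.802 × 10 × 0.0893 = 2.50 dB.
- Shares in the three lowest bands: 47.0, 50.3, 2.7% against 57.0, 41.6, 1.5%.
- Mean scores 0.557 and 0.445; variance 0.292.
- z = 0.1117 / √(2 × 0.292 / 251) = 2.32; power = Φ(0.36) = 64%.

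| Assumed mean, SD (normal) | Power on dB scale | Trend test on bands | Loss (points) |
|---|---|---|---|
| 10, 8 | 80% | 36% | 44 |
| 10, 10 | 80% | 44% | 36 |
| 15, 10 | 80% | 57% | 23 |
| 20, 10 | 80% | 64% | 16 |
| 25, 12 | 80% | 69% | 11 |
| 30, 15 | 80% | 71% | 9 |

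With lognormal dB HL (median 10 to 25, log-SD 0.4 to 0.6, by simulation) the full-scale comparison had 72 to 78% power and the loss ran from about 1 point (median 25, log-SD 0.6) to 54 points (median 10, log-SD 0.4).

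**Power, scenario B: fewer children have hearing loss (assumed).** Each arm mixes normal-hearing children (mean 10 to 12, SD 5 to 6) and children with loss (mean 28 to 35, SD 6 to 10). The share with loss falls from 40 to 29%, 30 to 20% or 20 to 12%. Over 12 simulated scenarios at 251 per arm, power was 39 to 67% for the trend test, 39 to 64% for the t test and 29 to 57% for the rank test. The trend test was never more than about 2 points below the t test and was up to 10 points above it. Two examples at 20 to 12% gave trend 61, t 51, rank 34, and trend 50, t 46, rank 32.

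**Sparse bands.** In scenario A the Profound band stays under 2% throughout, and the Severe band does so in all but one lognormal scenario (3.0%). The fallback would probably apply. It offers two routes, "e.g. combining like groups or applying a proportional odds model", without saying which, or which groups would be merged.

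**The case against.** The strongest objection is to any claim about power. A uniform shift is the form of effect that favours a mean or rank test over a threshold, and nothing in the plan says surgery timing acts that way. If it changes how many children have hearing loss, banding costs almost nothing and may help, while a rank test on dB can lose power. This stands: a reader might infer that the plan gives up a known amount of power, and the document does not support that.

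A reader might also infer that hearing at these ages gets no effect estimate at all. That is wrong: 7bi and 7bii carry a relative risk with 95% CI, and a change that leaves the better-ear average within its band can still move them. 7biii itself reports counts and percentages by arm, and one of the two fallback routes, the proportional odds model, would give an odds ratio.

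Finally, severity of hearing loss on a cited classification is a legitimate outcome, and a mean difference in dB answers another question. Nor is hearing the only domain without a full-scale measure: complications and middle ear function have none. These points tell against replacing 7biii. They do not tell against adding the dB difference, and they leave the missing effect measure for the bands where it was. The odds ratio appears only as one example in a conditional fallback.

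**Conclusion.** The point holds as a gap in what will be estimated. The four-frequency average is compared only through the Table 2 bands, no effect measure or interval is named for that comparison, and no hearing outcome at 3 or 5 years is compared in dB. This rests on the text alone.

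The size of any power loss rests on assumptions outside the document. It is roughly 10 to 50 points from 80% under a uniform shift (1 to 54 across all the distributions tried) and about nil against a t test if the share with hearing loss changes. That most children will fall in two bands is likewise an assumption: in the normal scenarios the two fullest bands held 76 to 100%. This is a secondary outcome with no stated power target. The case for a change is therefore interpretability: the trial should be able to say which hearing differences it excludes.

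**What to change.** - Keep the Table 2 severity comparison as planned.
- Add average dB HL at 3 and at 5 years to the continuous rows of Table 6. Report the between-group mean difference with a 95% CI, using a bootstrap interval if the data are skewed. Preferring the mean difference to a rank test avoids the loss seen in scenario B.
- Under Short ordinal outcomes, name an effect measure with 95% CI for the bands, for example the proportional odds ratio the section already mentions.
- Show the number tested by pure tone and by sound field in each arm. Treat a repeat in pure-tone children only as supportive, because whether a child can be tested that way is determined after randomisation.

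The cost is SAP wording and a few lines of code, since the average must already be computed to assign the bands. There are two drawbacks. The change adds two more estimates to a plan that does not adjust for multiplicity. And better-ear pure-tone and both-ears sound-field averages would share one scale, as they already do in Table 2.

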### Sample size

The sample size calculation was based on a test for proportions using a normal approximation: 292 participants per arm will allow a reduction in insufficient velopharyngeal function at 5 years from 40 to 29% to be detected with 80% power using a chi-squared test (2-sided significance test at 0.05 level). The estimate of 40% was obtained using data from a pilot trial of 50 5-year-old participants, conducted during the planning period for the grant application [18]. To allow an approximate attrition of 10%, 648 participants will be recruited. Restating the power for 300 participants per arm will allow the same difference to be detected with 81% power using a chi-squared test (2-sided significance test at 0.05 level). To consider the potential impact of variability around the value of 40%, 300 participants with valid data per group would provide 80% power to detect a reduction from 30 to 20% and 76% power to detect a reduction from 20 to 12%.

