## Trial status

The trial completed recruitment on 21 July 2015. In total, 558 patients from 22 centres were recruited and the last patient is due to attend their last visit on 30 July 2020. The analysis of outcomes will be conducted thereafter.

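### Power is restated for 300 children per arm, but recruitment closed at 558 in total, so none of the stated powers can be reached; about 74% to 78% is realistic for the target effect

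*SAP article*

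**What the plan says.** All the relevant statements are in the SAP article.

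- **Sample size, original design:** "292 participants per arm will allow a reduction in insufficient velopharyngeal function at 5 years from 40 to 29% to be detected with 80% power". The planned comparison is chi-squared, two-sided, with alpha 0.05.
- **Sample size, recruitment target:** "To allow an approximate attrition of 10%, 648 participants will be recruited".
- **Sample size, restated power:** "Restating the power for 300 participants per arm will allow the same difference to be detected with 81% power". For lower control-arm rates: "300 participants with valid data per group would provide 80% power to detect a reduction from 30 to 20% and 76% power". The 76% refers to the 20% versus 12% scenario.
- **Trial status:** recruitment was completed on 21 July 2015. "In total, 558 patients from 22 centres were recruited".
- **General analysis principles and Analysis of primary outcome:** only children with an observed outcome are analysed, nothing is imputed, and the primary analysis needs an eligible 5-year speech recording.

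No power is given for 558, and the article does not comment on the gap between 558 and 648.

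**The concern.** The article restates power at a size that its own Trial status section rules out. A recruited total of 558 is 90 below the target of 648, 42 below the 600 with valid data behind the restated powers, and 26 below the 584 needed for 80% power with no loss at all. Because the primary analysis uses only children with an eligible recording and does not impute, 558 is a ceiling on the number analysed.

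What is at stake is interpretation. A reader who takes the Sample size section at face value will put the chance of missing the target effect at 19% to 20%, and will give a non-significant result more weight as evidence against a benefit than the trial can support.

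**Working it through.** **Inputs.** Two-sided alpha 0.05, the three pairs of rates, 292 and 300 per arm, 648 and 10% attrition (Sample size); 1:1 allocation by minimisation with a random element (Trial design); 558 recruited (Trial status).

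**Formula.** Normal approximation for two proportions with n per arm, without continuity correction:

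- p̄ = (p1 + p2)/2
- SE0 = √[2·p̄(1 − p̄)/n]
- SE1 = √[(p1(1 − p1) + p2(1 − p2))/n]
- power = Φ[(p1 − p2 − 1.96·SE0)/SE1]

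**Step 1: reproduce the plan's figures.**

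- n for 40 vs 29% at 80% power: p̄ = 0.345, so n = [1.960·√(2·0.345·0.655) + 0.842·√(0.40·0.60 + 0.29·0.71)]² / 0.11² = 291.98, which gives 292 as stated.
- Recruitment: 648 × 0.9 / 2 = 291.6 per arm, consistent with 292.
- Power at 300 per arm, 40 vs 29%: SE0 = 0.03881, SE1 = 0.03855, (0.11 − 1.96 × 0.03881)/0.03855 = 0.880, Φ = 81.1% (stated 81%).
- At 300 per arm, 30 vs 20% gives 80.9% (stated 80%, which matches by truncation rather than rounding), and 20 vs 12% gives 76.3% (stated 76%).

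The formula is therefore consistent with the plan's own figures, and those figures are right for 300 per arm.

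**Step 2: per-arm size needed for each stated power.** 292 (80%) and 300 (81%) for 40 vs 29%; 294 (80%) for 30 vs 20%; 298 (76%) for 20 vs 12%. All exceed 558/2 = 279.

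**Step 3: power at the size recruited.** At 279 per arm, 40 vs 29%: SE0 = 0.04025, SE1 = 0.03998, (0.11 − 1.96 × 0.04025)/0.03998 = 0.778, Φ = 78.2%. At 10% loss, 558 × 0.9 = 502.2, about 251 per arm: SE0 = 0.04243, SE1 = 0.04215, (0.11 − 1.96 × 0.04243)/0.04215 = 0.637, Φ = 73.8%. The other rows follow in the same way.

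| Loss | n per arm | 40 vs 29% | 30 vs 20% | 20 vs 12% |
|---|---|---|---|---|
| As stated | 300 | 81% | 80% | 76% |
| 0% | 279 | 78.2% | 78.0% | 73.3% |
| 5% | 265 | 76.1% | 75.9% | 71.1% |
| 10% | 251 | 73.8% | 73.6% | 68.7% |

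The miss rate for 40 vs 29% is 100 − 78.2 = 21.8% with no loss and 100 − 73.8 = 26.2% at 10% loss.

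**Step 4: detectable difference.** From 40%, the rate detectable with 80% power is 28.8% at 279 per arm (11.2 points) and 28.2% at 251 per arm (11.8 points), against the planned 29% (11 points).

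**Step 5: checks on method and split.** Unpooled variance at 279 gives 78.6, 78.4 and 73.7%; a continuity correction gives 75.5, 75.0 and 69.3%. An uneven split such as 300 and 258, with no loss, gives about 78% for 40 vs 29%. None of these reaches a stated power.

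**The case against.** The strongest reply is that the Sample size section is a design rationale, that a plan normally preserves its design calculation, and that the 300-per-arm powers are conditional on having that many children with valid data. The actual recruitment is disclosed, the planned CONSORT chart will show the number analysed, and the relative risk with its 95% confidence interval will show the precision achieved. No test or decision rule depends on the power sentence.

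Much of this stands, and it limits the point. The 292 and 648 are legitimate as design history. The reason for stopping below 648 may be given in a fuller document, so its absence from an article is not a fault. But the article goes beyond history: it restates power at a new size, in prospective terms, although its own status section shows that size to be unattainable. Disclosing 558 elsewhere does not correct the figure.

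Three stronger readings should be resisted:

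- A reader might infer a calculation error. There is none; the powers reproduce at 300 per arm.
- A reader might infer that the miss rate at the size recruited is 26%. That figure needs the assumed 10% loss; with none it is about 22%. The article does not report actual attrition, and its section on missing data expects little.
- A reader might take 279 as a strict maximum for either arm. It assumes an even split, and minimisation with a random element can leave one arm slightly larger. Both arms cannot reach 292 or 300.

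**Conclusion.** The point holds: no power stated in the Sample size section can be delivered by a trial of 558. For 40 to 29%, power is about 74% to 78% instead of 80% to 81%; for 30 to 20%, about 74% to 78% instead of 80%; for 20 to 12%, about 69% to 73% instead of 76%. With complete follow-up the deficit is only 2 to 3 points; at the plan's own attrition allowance it is about 6 to 7 points. The range rests on the plan's assumed rates, an approximately even split, and 0% to 10% loss. The planned analysis itself is unaffected. The consequence is for how a non-significant result will be read, and the stated figures should be corrected because they are the ones a reader will rely on.

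**What to change.** In the Sample size section:

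1. Keep 292 per arm and 648 recruited, labelled as the original design, and state that 648 was not reached.
2. Replace the 300-per-arm powers with those for 558 recruited with 0% to 10% loss: about 78% to 74% for 40 to 29%, 78% to 74% for 30 to 20%, and 73% to 69% for 20 to 12%.
3. State that a non-significant result will be interpreted from the confidence interval against the target effect. Because the primary analysis reports a relative risk, either express the target on that scale (0.29/0.40 = 0.725) or add a confidence interval for the risk difference so that it can be set against the 11-point target.

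The cost is wording and a less favourable stated power. No extra children or data are needed, and the primary test does not change; a risk-difference interval, if chosen, is one added summary from the same two-by-two table.

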### Statistical analysis

#### General analysis principles

Three analysis populations will be considered: the intention-to-treat (ITT), the per-protocol (PP), and the safety population.

The principle of ITT, as far as practically possible, will be the main strategy of the analysis adopted for the primary outcome and all the secondary outcomes. These analyses will be conducted on all randomised participants, in the group to which they were allocated, and for whom the outcomes of interest have been observed/measured. No imputations are planned.

A per-protocol analysis, which will mirror the ITT population but exclude participants defined as having a major protocol deviation, will only be considered in the event of major protocol deviations in more than 10% of the ITT analysis population and apply to a secondary analysis of the primary outcome only. Table S1 provides a list of the protocol deviations.

The safety dataset will classify participants who have surgery before 9 months of gestational corrected age as received 6 months surgery, and surgery at 9 months of gestational corrected age or beyond as received surgery at 12 months.

A *p* value of 0.05 or less will be used to declare statistical significance for all analyses; *p* values will be reported to two significant figures. Rather than adjust for multiplicity, relevant results from other studies already reported in the literature will be taken into account when interpreting the study. Percentages will be presented to one decimal place, and continuous summary statistics will be given to a maximum of two decimal places.

All analyses will be performed using standard statistical software (SAS 9.4 or later). The finalised analysis datasets, programs, and outputs will be archived following Good Clinical Practice guidelines and standard operating procedures at the Liverpool Clinical Trials Centre.

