#### Lost to follow-up, withdrawals, and missing data

The timing of withdrawal in relation to surgery and scheduled visits, level of withdrawal, who made the decision, and reason for withdrawal will be summarised both overall and for each randomised group. Frequencies will be presented along with percentages using the number of participants who withdrew as the denominator.

The number lost to follow-up both overall and within each randomised group will be reported, and the reasons where known will be documented. Any deaths and their causes will be reported separately.

Based on experience from the ScandCleft study, the structure of the centralised cleft palate care system and trial-specific systems in place will ensure the occurrence of missing data is likely to be low. Therefore, the potential impact of any missing data is likely to be low. For all assessments and outcomes, participants with insufficient data to make their assessments will be expressed as a frequency and a percentage with the denominator being those who were randomised, treated, and consented.

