#### Adherence

Reasons for participants not receiving the randomised allocation will be summarised in a table. Adherence with follow-up time points (30 days, 12 months, 3 and 5 years) will be summarised at the visit level (at least one scheduled assessment visit completed per time point) and assessment level, which will specify adherence to specific assessments. When applicable, whether or not assessments were made within the expected window (Table 5) will be presented. Summaries will be presented both overall and for each randomised group.

**Table 5 Tab5:** Follow-up visits: estimated visit dates and corresponding window limits

Time point	Estimated visit date, calculated from date of birth	Window limits of estimated visit date	
		Earliest	Latest
12 months	52 weeks^1^	*6 months arm:* − 4 weeks	+ 48 weeks (equivalent to 23 months of age)^2^
		*12 months arm:* − 2 weeks	
3 years	156 weeks	− 4 weeks	+ 48 weeks (equivalent to 3 years 11 months of age)
5 years	260 weeks	− 4 weeks	+ 48 weeks (equivalent to 5 years 11 months of age)

^1^Corrected for gestational age. Full term is defined as day 1 of the 40th week of pregnancy

^2^Speech assessments vary in their latest acceptable date:

• Six months surgery patients should have their speech assessed by + 26 weeks (equivalent to 18 months of age)

• Twelve months surgery should have their speech assessed before surgery

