#### Safety evaluations

Serious adverse events and unanticipated problems will be presented using descriptive statistics. Line listings of events will also be presented to provide further detail. Patients will be reported according to the safety dataset, with the number of events and patients in each safety group summarised. Tests of statistical significance will not be undertaken; rather, the clinical importance of any imbalance will be noted.

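### Serious adverse events are summarised only by age at surgery, so an illness-delayed child changes column, a never-operated child has none, and no table by randomised group is planned

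*SAP article*

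**What the plan says.** Three statements in the SAP article fix how SAEs are grouped.

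- General analysis principles defines the safety dataset by age at operation: "The safety dataset will classify participants who have surgery before 9 months of gestational corrected age as received 6 months surgery". Any operation from that age onwards puts the child in the 12-month class. There is no third class and no fallback to the allocated group.
- Safety evaluations applies that dataset to SAEs and unanticipated problems: "Patients will be reported according to the safety dataset, with the number of events and patients in each safety group summarised". It adds that "Line listings of events will also be presented to provide further detail". It does not say whether an event must begin before or after the operation to be counted, and it plans no summary by allocated arm. Imbalances are to be judged clinically, without significance tests.
- General analysis principles states that intention to treat "will be the main strategy of the analysis adopted for the primary outcome and all the secondary outcomes". SAEs are not in the list of secondary outcomes, so that rule does not reach them.

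The article expects departures from the ideal course. Under Adherence, "Reasons for participants not receiving the randomised allocation will be summarised in a table". Under Lost to follow-up, withdrawals, and missing data, "The timing of withdrawal in relation to surgery and scheduled visits" is to be summarised by randomised group, and deaths and their causes are to be reported separately.

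**The concern.** Age at surgery is known only after randomisation, and a serious illness can change it. Suppose a child allocated to 6 months falls ill and is operated on at 9 months or later. The rule then counts that child under 12-month surgery. If the illness was itself a reportable SAE, it goes to the 12-month column too. A child allocated to 12 months whose operation is delayed stays where they were, so delay through illness moves children in one direction only.

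A child who is never operated on meets neither definition. Any SAE in that child has no place in the two-column summary, although it may appear in the listings.

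At stake is the reading of the SAE table. It is to be interpreted by clinical judgement of any imbalance, and without a table by randomised group the reader cannot tell a difference between the timings from a difference made by the grouping rule.

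**Working it through.** The plan states no figure on this point, so there is none to reproduce. The check is of the text, followed by an illustration of size.

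**Text.** The cases are set against the rule as written:

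| Allocated | What happens | Safety column |
|---|---|---|
| 6 months | Operated before 9 months | 6 months |
| 6 months | Illness delays surgery to 9 months or later | 12 months |
| 12 months | Operated at 9 months or later, delayed or not | 12 months |
| Either | Never operated | None |

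If every child is operated on and none crosses 9 months in either direction, the safety table is identical to the table by randomised group. The difference comes entirely from children who cross and children never operated on.

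**Inputs for the illustration.**
- From the article: 558 recruited (Trial status) and 1:1 allocation (Trial design). An exactly equal split is assumed: 558 / 2 = 279 per arm.
- Assumed, because the article gives no values: s children per arm with at least one SAE, equal in both arms (true ratio 1.00), and m of those in the 6-month arm operated on at 9 months or later because of a pre-surgery SAE that is reportable.

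**Formula.** Tabulated risk is (s − m)/(279 − m) in the 6-month column and (s + m)/(279 + m) in the 12-month column.

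| s per arm | m | 6-month column | 12-month column | Ratio |
|---|---|---|---|---|
| 8 (about 3%) | 1 | 7/278 = 2.5% | 9/280 = 3.2% | 0.78 |
| 8 | 4 | 4/275 = 1.5% | 12/283 = 4.2% | 0.34 |
| 14 (about 5%) | 1 | 13/278 = 4.7% | 15/280 = 5.4% | 0.87 |
| 14 | 4 | 10/275 = 3.6% | 18/283 = 6.4% | 0.57 |
| 14 | 7 | 7/272 = 2.6% | 21/286 = 7.3% | 0.35 |
| 28 (about 10%) | 3 | 25/276 = 9.1% | 31/282 = 11.0% | 0.82 |
| 28 | 5 | 23/274 = 8.4% | 33/284 = 11.6% | 0.72 |
| 28 | 10 | 18/269 = 6.7% | 38/289 = 13.1% | 0.51 |

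Tabulated by randomised group, every row would give s/279 in both arms, a ratio of 1.00. The rows with m at a third to a half of s are extremes. The rows with m = 1 to 3 show that a few children are enough to produce a visible difference.

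**Never-operated children.** If 2% to 5% were never operated on (assumed), 0.02 × 558 = 11 to 0.05 × 558 = 28 children have no column. Only those with an SAE affect the summary. At an assumed 10% SAE risk that is about 1 to 3 children.

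**The case against.** The strongest reply is that the effect needs pre-surgery SAEs to be reportable, and the article gives no reporting period. That is commonly left to the protocol, which is not shown. If reporting begins only at surgery, the illness that caused the delay is never counted and a never-operated child has no reportable event. What remains is small: a delayed child's later events are attributed to the surgery received. This stands, and it is why no size can be claimed.

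As-treated grouping is also conventional for events that surgery may cause. That stands too. The point is that it is the only SAE summary, not that it is used.

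A reader might infer that the trial's safety objective is compromised. The article does not support that. Outcome 6 (dehiscence, infection and fistula) is its named measure of procedural safety and is analysed by allocated group. Table 4 presents intra-operative events, early complications and 48-hour observations by randomised group as well.

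A reader might also infer that events in never-operated children disappear. The line listings are not expressly limited to operated children, deaths are reported separately, and withdrawals and reasons for not receiving the allocation are summarised. These limit the loss, but none of them is an SAE comparison by arm.

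**Conclusion.** The point holds in a limited form. SAEs and unanticipated problems are summarised only in groups that depend on a post-randomisation event. Delay through illness can only move events from the 6-month to the 12-month column, and a never-operated child has no column.

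The size is unknown. It rests on the reporting period and on how many children are affected, and neither is in the article. The ratios shown are conditional on assumed SAE risks and crossing numbers and do not estimate what the trial will show.

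Two stronger readings should be resisted. The first is that the whole table favours 6-month surgery. Only the crossing mechanism has a clear direction, and leaving out never-operated children could act either way. The second is that the longer wait before surgery in the 12-month arm is itself a bias. If both arms are observed over the same period from randomisation and nobody crosses, the table equals the randomised comparison.

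This is a cheap improvement to one descriptive display. It leaves the primary analysis and the secondary outcomes untouched.

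**What to change.** In Safety evaluations:

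1. Add a descriptive table of SAEs and unanticipated problems, giving events and patients by randomised group for all randomised children, including those never operated on.
2. Keep the safety-dataset table as a second display, limited to events on or after the date of surgery.

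The first table removes the dependence on age at surgery whatever the reporting period turns out to be, and it gives never-operated children a place. The second keeps the attribution of post-operative events to the surgery received.

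The cost is a change of wording and one further descriptive table from data already held. No hypothesis test or clinical rule changes. The downside is that safety results appear in two groupings, so each table needs a clear label.
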